### Concomitant medications

All concomitant drug therapies received will be recorded at baseline and follow-up assessments.

Interactions include the following:Live attenuated virus vaccines. Immunoglobulin administration may impair for a period of at least 6 weeks and up to 3 months the efficacy of live attenuated virus vaccines such as measles, rubella, mumps and varicella. After administration of this product, an interval of 3 months should elapse before vaccination with live attenuated virus vaccines. In the case of measles, this impairment may persist for up to 1 year. Therefore, patients receiving measles vaccine should have their antibody status checked.Interference with serological testing. After injection of immunoglobulin the transitory rise of the various passively transferred antibodies in the patient’s blood may result in misleading positive results in serological testing. Passive transmission of antibodies to erythrocyte antigens, for example, A, B, and D, may interfere with some serological tests including the antiglobulin test (Coomb’s test).

Details of all other agents that might interact with IntratectTM can be found in the British National Formulary (BNF) (http://www.bnf.org/bnf/).

Study site investigators and patients will be provided with an emergency 24-hr unblinding contact number.

Participants should not receive any other investigational drugs or agents during their participation in the study.

Should patients experience a flare-up of their CRPS pain or a trial intervention-induced reduction in pain level, they may, in discussion with their PI (or a delegated experienced pain specialist), increase or reduce the dose of their current medications.

### Safety monitoring

The following blood tests will be done at baseline only. Additional blood monitoring is only required for the protocol in response to adverse events.

#### Routine haematology

Routine haematology includes the following:white blood cell and differential count (eosinophils, basophils, neutrophils, lymphocytes and monocytes);red blood cell and indices ( PCV, MCV, MCH , MCHC);haemoglobin;platelets;serum IgA;serum IgM; andserum IgG.

#### Biochemistry

Routine biochemistry includes:sodium;potassium;urea;serum creatinine; andALT, AST, GGT, bilirubin.

#### Pregnancy

Pregnancy status will be verified using blood pregnancy testing at baseline for female patients of childbearing potential and urine pregnancy testing at visit 4 if patient is receiving open-label IntratectTM.

### Randomisation

#### Identification and randomisation of patients

A patient identification number will be allocated by registering the patient on the MACRO eCRF system after consent has been signed. The system will generate a unique identifier to be used throughout the study.

Patients will be allocated (on study day 0) to placebo or IVIg (ratio 1:1) by sites via an online system based at the King’s Clinical Trials Unit (King’s CTU), based at the Institute of Psychiatry. Allocation will be at the level of the individual patient via block randomisation with randomly varying block sizes, stratified by centre.

Only site staff authorised to request randomisation will receive passwords for the randomisation system. Requests for passwords are via the trial manager of the King’s CTU.

### Implementation procedures

Sites will be responsible for maintaining a baseline of ‘in date’ stock on shelf of both active and placebo IMPs.

Unblinded bottles for the open-label phase of the study will also be available and supplied to participating sites.

Once an eligible patient has provided written informed consent and completed the baseline assessments, he/she will be asked to complete pain diaries daily after the screening visit until the infusion visit. The study site investigator will contact the patient by telephone at an agreed time between 8 and 14 days after the screening visit and collect screening pain diary scores. If the patient is eligible on pain diary and blood results, an infusion visit will be scheduled.

Online randomisation will be requested by site one day prior to the infusion. Patients can only be randomised after the allocated study site nurse has confirmed by telephone a) that the patient is well, b) that the patient is willing and able to come to the infusion unit the next day, c) the details of the arranged transport, d) any anticipated problems from the patient’s perspective, and e) that the pharmacy will be able to dispense in good time.

The randomisation system will automatically generate two emails at the point of randomisation. The first will be sent to appropriate members of the study team, who are blinded to treatment allocation, and will just confirm that the patient has been randomised. The second will be sent to the dispensing pharmacy to inform them of the treatment allocation and will be copied to the eSMS emergency code break service, so they have the unblinding information available in the event of the need to unblind. A study-specific prescription will be completed (for dosing schedule, see Table 1) and sent to the pharmacy for dispensing. The dispensing pharmacist will refer to the randomisation email when the prescription is received. Any bottle of IMP in the appropriate trial arm can be selected for dispensing but if IMP is available with an earlier expiry this should be used in preference to IMP with a later expiry.

### Blinding

The trial will be double blinded. Blinding will be achieved by preparing both study drug and placebo (0.1% albumin in normal saline) solution into identical-looking bottles. Batch numbers and expiry dates for both active and placebo drug will be indistinguishable.

The IMP will be supplied directly to designated pharmacy contacts at participating sites. The tear-off section on the primary container (bottle) and the secondary packing will inform the dispensing site pharmacy of the true nature of contents (Active or Placebo). At dispensing, this section of label is removed to maintain blinding.

In the event of an urgent need to unblind treatment, the 24-hour emergency code break service must be contacted This should be the preferred route to code break, even in office hours when the site pharmacist is available, as there is then a full audit trail of the code break event. The site pharmacy will also be aware of the patient’s treatment allocation.

Unblinding should only occur where knowledge of the randomised treatment is needed for immediate patient care and cannot be delayed until the next working day when the study team can be contacted. Code breaks will not be routinely opened for participants who complete study treatment.

If a request for code break is received from a physician (for example, the patient’s general practitioner) outside the research team, Guy’s Medical Toxicology Unit (eSMS) will attempt to contact the research team to verify the request before the code is broken.

If the code is broken, details including patient study number, the date code break was performed, the person who broke the code, and the reason for the code break, shall be recorded by the emergency code break service and retained. The trial manager will be informed of the unblinding event. If clinically indicated, the participant will be withdrawn from the study medication.

Accidental unblindings will be dealt with on a case by case basis if and when they arise. The patient’s data should continue to be collected according to the visit schedule, even in the event of unblinding or withdrawal from study medication, unless the patient refuses.

### Study data

#### Trial database

An electronic Case Report Form (eCRF) will be created using the InferMed Macro system. This system is regulatory compliant (GCP, 21CRF11, EC Clinical Trial Directive). The eCRF will be created in collaboration with the trial statisticians and the investigators and will be maintained by the King’s Clinical Trials Unit. It will be hosted on a dedicated secure server within KCL.

Source data will be entered by authorised staff onto the eCRF with a full audit trail.

### Database passwords, data handling and confidentiality/format of records

Database access will be strictly restricted through passwords to the authorised research team.

Data will be handled, computerised and stored in accordance with the Data Protection Act, 1998. Participants will be identified on the study database using a unique code and initials. The investigator will maintain accurate patient records/results detailing observations on each patient enrolled. All participant contact/screening and recruitment data will be will be stored on spreadsheets within the recruiting NHS sites, which will have restricted access from password protected computers. Accrual data uploaded to the UKCRN portfolio database will be anonymised and collated by the Trial Manager to CLRN. No identifiable data will be entered on the eCRF or transferred to the coordinating CTU.

At the end of the study, essential documentation will be archived in accordance with sponsor and local requirements. The retention of study data will be the responsibility of the Chief Investigator.

### On-site/central monitoring

The Trial Manager will conduct on-site/central monitoring. The Data Manager/Statistician may identify data fields that should be checked against the source data during site monitoring visits, the specifics will be outlined in a Data Management standard operating procedure (SOP). Where there are data queries, the research nurses will be responsible for resolving the queries. The Trial Manager will review responses before closing the query.

### Statistical considerations

Data analysis will be performed by the study statistician at University College London, using a password-protected computer in a private office.

### Statistical analysis

A comprehensive statistical analysis plan will be developed and agreed upon with the trial’s oversight committees. Descriptive analysis (for example, summary statistics and plots) will be performed to investigate the distribution of the primary outcome, pain score, across participants.

#### Efficacy

##### Primary analysis

The primary outcome will be analysed using a mixed model to establish any difference between pain scores after IVIg and placebo. The stratification factor (centres) will be a fixed effect. The model will efficiently model the repeated measurements data. Modelling assumptions will be checked (for example, residuals). All analyses will be performed on an intention-to-treat basis. Every effort will be made to reduce loss to follow-up (using phone calls *etcetera*). Participants who do not contribute any outcome measurements for the primary outcome will be omitted from the analysis. Participants who provide any outcome data will be included. No imputation will be performed.

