### Subject population

#### Inclusion criteria

Diagnosis of Complex Regional Pain Syndrome I or II according to Budapest research criteria (Additional file 2) [22]Disease duration of 1 to 5 years and a mean pain intensity on an 11-point (0 to 10) Numeric Rating Scale (NRS) over the first seven daily entries after screening within a pre-defined range (see section 9 for details of pain thresholds for eligibility)Failure to respond (poor efficacy or unacceptable side effects) to drugs recommended for the treatment of neuropathic pain [23], including pregabalin or gabapentin, tricyclic antidepressants, and mild and strong opioids (where not contraindicated or refused by the patient).Previous specialised pain physiotherapy [24] (where not contraindicated or refused by the patient)Willingness to confirm the use of adequate birth control while on the trial will be required in premenopausal women without evidence for an inability to become pregnant.Willingness to not start any other treatment for CRPS during the parallel part of the trialAge 18 years and above

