##### Secondary analysis

As a secondary analysis, we will calculate the proportion of patients in each arm who achieve 50% or 30% pain relief (based on the average pain level entered on day 6 to 42), compared to their baseline level of pain (the average pain level recorded during the first 7 days of the screening period). Using these proportions, we will calculate the number needed to treat (NNT) with IVIg, so that one additional patient will achieve 50% pain relief.

Possible changes in treatment effect over time and association between disease duration, psychological baseline measurements, allergy status, low baseline IgG plasma level, IgG increase, and treatment response, as well as any association between psychological measurements with the primary outcome, will be investigated using exploratory plots and regression models with interaction terms. Change in the McGill Pain Questionnaire (Short Form) descriptor terms [25] limb temperature and QST changes before-after IVIg/placebo treatments on affected/contra lateral sides, pain interference and quality of life (QoL) outcomes will be investigated using either standard regression models or mixed models. In those who decide to receive both open infusions, and who have at least 30% or 2 NRS points average pain relief from 6 to 20 days after their last open infusion as compared with baseline, the time between the last open infusion and the first period with average weekly pain equalling or exceeding baseline -1NRS point) is calculated as the IVIg effect duration. As the study ends on day 148 (12 weeks after the second open infusion), later effects will not be recorded.

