### Sample size calculation

The sample size was calculated as follows: 122 participants are required to detect a difference in pain score of 1.2 using a two-sample t-test assuming 5% statistical significance, 85% power and a common standard deviation of 2.2 (as in our previous study (8)). Assuming 10% loss to follow-up and 5% noncompliance increases, this number increases to 152 participants. We actually intend to collect 37 measurements of pain intensity (the primary outcome) per participant and analyse the outcome using a mixed-effects regression model.

Thus we can reduce this sample size based on these extra measurements. The correlation among a patient’s measures is assumed to be 0.7 (from our previous study), and hence, the multiplying factor is as follows:

Therefore, the total required sample size is 152 × 0.71 = 108 participants [26].

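### The stated primary mixed model names centre as its only covariate and leaves out the baseline pain mean already collected before randomisation, which costs precision but not validity

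*Protocol article*

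**What the plan says.** The Primary analysis section describes the model in these terms: "The primary outcome will be analysed using a mixed model to establish any difference between pain scores after IVIg and placebo". On covariates it says: "The stratification factor (centres) will be a fixed effect". It names no other covariate.

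Baseline pain is measured and defined elsewhere. The Inclusion criteria require a mean NRS "over the first seven daily entries after screening within a pre-defined range". The Secondary analysis section takes as baseline "the average pain level recorded during the first 7 days of the screening period" and uses it for the 30% and 50% responder proportions; effect duration in the open phase is also judged against baseline. None of these places puts it in the primary model.

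Randomisation is "block randomisation with randomly varying block sizes, stratified by centre", so the design does not balance baseline pain between arms.

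The Sample size calculation starts from this statement: "122 participants are required to detect a difference in pain score of 1.2 using a two-sample t-test". Its other inputs are a significance level of 5%, power of 85% and an SD of 2.2 in both arms. It inflates to 152 for 10% loss to follow-up and 5% non-compliance. It then multiplies by 0.71 to reach 108, because 37 pain measurements per patient with correlation 0.7 will be analysed.

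**The concern.** Pain before and after treatment is measured on the same 0 to 10 scale in the same patients. A pre-randomisation mean of seven daily scores would be expected to explain some of the between-patient variation in the follow-up mean. A model without it leaves that variation in the error term.

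The abstract gives the primary objective as confirming efficacy and determining the effect size with confidence, so the width of the confidence interval is part of what the trial is meant to deliver. With 54 patients per arm and stratification by centre alone, the arms may also differ by chance in baseline pain. In an unadjusted analysis, such a difference carries into the estimate in proportion to the association between baseline and outcome.

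**Working it through.** **Inputs from the protocol** (Sample size calculation, unless noted): difference 1.2; SD 2.2; 5% significance (two-sided reproduces the figure); power 85%; loss 10%; non-compliance 5%; 37 follow-up measurements; within-patient correlation 0.7; 54 per arm (Methods/Design); 7 baseline days (Secondary analysis).

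**Step 1. Reproduce 108.**
- Two-sample formula: 2 × (1.960 + 1.036)² × (2.2/1.2)² = 60.4, so 61 per arm and 122 in total, as stated.
- Inflation: 122 / 0.90 / 0.95² = 150.2. Rounding up to an even number at each step gives the stated 152.
- Factor for the mean of 37 follow-up values: (1 + 36 × 0.7)/37 = 0.708.
- 152 × 0.71 = 107.9, so 108.

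The factor 0.708 is the variance of a follow-up mean relative to a single value, and it contains no baseline term. The sample size and the stated model therefore describe the same unadjusted analysis.

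**Step 2. Unadjusted precision on the planning figures.**
- SD of the 37-day mean: 2.2 × √0.708 = 1.85.
- Patients with data: 54 × 0.90 = 48.6 per arm.
- Effect after 5% non-compliance: 1.2 × 0.95 = 1.14.
- SE of the difference: 1.85 × √(2/48.6) = 0.376.
- 95% half-width (normal approximation): 1.96 × 0.376 = 0.74.
- Power (two-sample t-test): 85.2%.

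**Step 3. Add the baseline mean.** If *r* is the correlation between the 7-day baseline mean and the 37-day follow-up mean, adjustment multiplies the variance of the treatment difference by (1 − *r*²). The protocol does not give *r*, so the values below are assumptions.

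| Assumed *r* | 1 − *r*² | Fall in variance | SE | 95% half-width | Power |
|---|---|---|---|---|---|
| none (as stated) | 1.00 | – | 0.376 | 0.74 | 85% |
| 0.3 | 0.91 | 9% | 0.358 | 0.70 | 88% |
| 0.5 | 0.75 | 25% | 0.325 | 0.64 | 93% |
| 0.7 | 0.51 | 49% | 0.268 | 0.53 | 99% |

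Half-widths based on the t distribution are about 0.01 larger.

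**Step 4. Ceiling from the protocol's own correlation.** Suppose 0.7 held equally between every baseline day and every follow-up day. The relative variance of the 7-day mean would be (1 + 6 × 0.7)/7 = 0.743, and *r* would be 0.7/√(0.743 × 0.708) = 0.97. This is an idealised upper limit only. Eligibility confines baseline means to a range, which lowers the correlation. Screening may fall on day −21 and follow-up runs to day 42, so the days compared can lie up to nine weeks apart, and correlation usually decays over such a gap.

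**The case against.** The strongest reply is that the Primary analysis section is a summary. It does not call centre the only covariate, it also leaves out the time terms and covariance structure, and the Statistical analysis section promises a comprehensive analysis plan that is not at hand. That plan may include baseline pain. This stands as a limit: the point concerns the model as the protocol states it, and a reader should not infer that the trial team decided to exclude baseline. It does not remove the point. The protocol did choose to name a covariate, and the sample-size factor, which has no baseline term, agrees with the model as written.

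The second reply is that nothing stated is wrong. The sample-size figures reproduce, randomisation makes the unadjusted estimate unbiased, and the confidence interval already covers chance imbalance as sampling variation. All of that is correct. A reader might infer that the primary comparison is biased or the trial underpowered, but the documents support neither.

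The third reply is that the gain is assumed. That too is correct. The 0.7 is stated among a patient's repeated measures and comes from the earlier single-centre crossover trial with 13 patients. It cannot be carried over to baseline days as an estimate, and 0.97 must not be read as the expected correlation. Nor do the documents show that baseline pain is the strongest predictor of outcome, or that 0.3 to 0.7 is a conservative range. At 0.3 the gain is modest: three percentage points of power and 0.04 NRS points of half-width.

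**Conclusion.** The concern holds as a loss of precision. As stated, the primary model and the sample size both leave out a baseline pain mean that every eligible patient should have before randomisation. Following the protocol gives a valid estimate with about 85% power. The same data, adjusted for baseline, would give a narrower interval: about 5% narrower at an assumed correlation of 0.3 (0.70 against 0.74) and 29% narrower at 0.7 (0.53 against 0.74).

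These sizes rest on the protocol's SD, correlation and loss assumptions, and on a correlation between baseline and follow-up means that it does not give. The change should be made because it serves the stated aim of determining the effect size, but the trial does not depend on it.

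**What to change.** State in the primary analysis, before unblinding, that the mixed model includes treatment, centre and the mean baseline NRS over the first 7 screening diary days, entered as a continuous variable, as fixed effects. This is the protocol's own baseline definition, so the responder analysis and the primary model would share one baseline.

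Do not widen the covariate to all diary days before infusion. Under Implementation procedures, "he/she will be asked to complete pain diaries daily after the screening visit until the infusion visit". Randomisation is on day 0, the first infusion is planned for day 1, and it may slip to day 5, so such a mean could include entries made after randomisation.

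The cost is one sentence, with no new data and no more patients. The target of 108 can stay as it is. If the analysis plan already adjusts for baseline pain, the two documents only need to be aligned.

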##### Secondary analysis

As a secondary analysis, we will calculate the proportion of patients in each arm who achieve 50% or 30% pain relief (based on the average pain level entered on day 6 to 42), compared to their baseline level of pain (the average pain level recorded during the first 7 days of the screening period). Using these proportions, we will calculate the number needed to treat (NNT) with IVIg, so that one additional patient will achieve 50% pain relief.

Possible changes in treatment effect over time and association between disease duration, psychological baseline measurements, allergy status, low baseline IgG plasma level, IgG increase, and treatment response, as well as any association between psychological measurements with the primary outcome, will be investigated using exploratory plots and regression models with interaction terms. Change in the McGill Pain Questionnaire (Short Form) descriptor terms [25] limb temperature and QST changes before-after IVIg/placebo treatments on affected/contra lateral sides, pain interference and quality of life (QoL) outcomes will be investigated using either standard regression models or mixed models. In those who decide to receive both open infusions, and who have at least 30% or 2 NRS points average pain relief from 6 to 20 days after their last open infusion as compared with baseline, the time between the last open infusion and the first period with average weekly pain equalling or exceeding baseline -1NRS point) is calculated as the IVIg effect duration. As the study ends on day 148 (12 weeks after the second open infusion), later effects will not be recorded.

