Secondary objectives are to achieve a better understanding of this technology including the following:stability of effect with repeat administration;factors predicting a beneficial response;effects on additional outcome parameters including stimulus evoked pain, pain interference, quality of life, and short-term risk profile;health economics evaluation; andcreation of a bank of biological samples for future complex regional pain syndrome research.

The primary outcome will be the average 24-h pain intensity over 37 days (to be completed on day 6 to day 42 after randomisation to record pain intensity during the previous 24 hours).

The number of study sites will be seven: all UK-based specialist pain clinics in secondary care (Liverpool, London, Bath, Glasgow, Norfolk and Norwich, Cambridge, Leicester).

The study population size will be 108 (54 in each study arm).

The study duration will be 44 months (from study set-up to analysis).

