### Research blood samples

Research blood samples will be requested at baseline and day 43. Patients not consenting to provide research blood samples may still be randomised into the study. Patients only willing to provide research blood samples on a single occasion will just have the first sample taken.

On consenting patients, 30 ml of blood will be collected in a gel tube and centrifuged at 2,000 G for 10 minutes according to local policy (no specific centrifuge protocol is required). Serum must then be pipetted or poured into 10-ml aliquots and stored frozen in a -20 or -80 freezer. Each aliquot must be labelled with the patients study PIN, initials, date of birth and date of sample collection. Details of sample collection must be entered on the eCRF system.

The blood samples will be used to examine serum antibodies, mediators or substances in patients with complex regional pain syndrome. Samples will be stored and examined for 30 years.

On a periodic basis, the study monitor will arrange for a shipment of dry ice to be delivered to the study site and for samples to be shipped via courier to the University of Liverpool on the same day. Shipment forms will be provided to sites by the study monitor.

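### IgG increase, a consequence of receiving IVIg, is listed with pre-randomisation factors for the treatment-response interaction models; it belongs in a separate analysis within the IVIg arm

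*Protocol article*

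**What the plan says.** The secondary objectives, at the end of the Background of the protocol article, include finding "factors predicting a beneficial response". The Secondary analysis section takes this up. It names disease duration, psychological baseline measurements and allergy status, and continues with "low baseline IgG plasma level, IgG increase, and treatment response". Together with changes in treatment effect over time and associations of psychological measures with the primary outcome, these "will be investigated using exploratory plots and regression models with interaction terms".

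Two places bear on how an IgG increase could be measured:

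- **Safety monitoring** introduces the laboratory panel with "The following blood tests will be done at baseline only" and adds "Additional blood monitoring is only required for the protocol in response to adverse events". The Routine haematology list that follows ends with "serum IgM; andserum IgG".
- **Research blood samples** states "Research blood samples will be requested at baseline and day 43". Sampling is optional, and a patient who agrees to only one sample gives only the first. On purpose it says "The blood samples will be used to examine serum antibodies, mediators or substances in patients with complex regional pain syndrome".

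Blinded infusions are on days 1 and 22. The comparator is 0.1% albumin in normal saline. The primary outcome uses diary entries from days 6 to 42.

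**The concern.** Every other listed factor describes the patient before treatment. Randomisation balances such factors in expectation, so a treatment-by-factor interaction compares randomised arms at each level of the factor and can be read as a difference in treatment effect.

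IgG increase has no such reading. One arm is infused with immunoglobulin and the other is not, so the size of the rise is largely decided by allocation. Patients in the two arms with the same IgG change are not comparable groups: for a treated patient that value reflects how the infused product was received and cleared, and for a placebo patient it reflects natural variation. If whatever governs the rise in treated patients also relates to their pain prognosis, the slopes of pain on IgG change will differ by arm even when IVIg has the same effect in everyone.

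At stake is the interpretation of one exploratory result under a secondary objective. A significant term could be reported as a predictor of benefit when it is not one.

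**Working it through.** **1. Is the variable pre- or post-randomisation?** The article gives no figure for this point, so the first check sets the passages side by side.

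| Listed factor | When it is known | Can the allocated treatment change it? |
|---|---|---|
| Disease duration | before randomisation | no |
| Psychological baseline measurements | before randomisation | no |
| Allergy status | before randomisation | no |
| Low baseline IgG | before randomisation | no |
| IgG increase | after infusion | yes, IVIg is immunoglobulin |

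**2. Where could a follow-up value come from?** The routine panel gives IgG at baseline only. The only later scheduled blood sample that the article describes is the optional research serum at day 43. That is 43 − 22 = 21 days after the second infusion and 43 − 42 = 1 day after the outcome window closes. The rise would therefore be measured once the outcome is complete, and only in patients who gave both samples.

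**3. Can an interaction appear without effect modification?** A simulation of 1,500 trials per setting used these inputs.

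*From the article:*
- 108 patients, allocated 1:1, so 54 per arm.
- A treatment effect of 1.2 NRS points and an SD of 2.2.
- Correlation 0.7 over 37 measurements. The variance factor is (1 + 36 × 0.7)/37 = 26.2/37 = 0.708, which agrees with the article's 0.71. The variance of a patient's mean pain is then 2.2² × 0.708 = 3.427, and its SD is 1.851.

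*Assumed:*
- The effect is −1.2 in every patient, so there is no effect modification.
- A latent prognosis correlates 0.5 with pain.
- In the IVIg arm, IgG change correlates *r* with that prognosis. On placebo it is unrelated to it.
- IgG change has SD 1 in each arm and is shifted upward by 1, 2 or 4 SD on IVIg.

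The model contained arm, IgG change and their product. Rejection rates for the product term at nominal 5% were:

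| Shift on IVIg | r = 0 | r = 0.5 | r = 0.8 |
|---|---|---|---|
| 1 SD | 4.5% | 25.3% | 57.3% |
| 2 SD | 4.4% | 24.8% | 56.1% |
| 4 SD | 4.7% | 24.7% | 57.2% |

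**4. Check by formula.** The expected difference in slopes is SD × 0.5 × *r*. The residual variance averaged over the two arms is 3.427 × [1 + 1 − (0.5*r*)²]/2, and the standard error of the slope difference is about √(2 × that variance/54).

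- *r* = 0.5: slope difference 1.851 × 0.25 = 0.463. Variance 3.427 × 0.969 = 3.320, standard error √(6.640/54) = 0.351, ratio 1.32. Against a critical value of 1.98, power is about 25%.
- *r* = 0.8: slope difference 1.851 × 0.40 = 0.740. Variance 3.427 × 0.92 = 3.153, standard error √(6.306/54) = 0.342, ratio 2.17. Power is about 57%.

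Both agree with the simulation. The shift does not enter the formula, which is why the rows of the table barely differ. The excess rejections come only from the assumed confounding in the IVIg arm.

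**The case against.** The strongest reply is that the article does not write down the model being criticised. One method phrase covers several aims, and the sentence does not say which variables receive a treatment interaction. IgG increase could be handled by a plot, or by a regression within the IVIg arm. A comprehensive statistical analysis plan is promised, the work is labelled exploratory, and neither the primary analysis nor the sample size depends on IgG.

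Much of this stands. That a treatment-by-IgG-increase term will be fitted is the plain reading, not an explicit statement. The point is still more than missing detail: the article itself chose to put a treatment consequence in one series with baseline factors, under one method and one objective. An exploratory label does not turn a post-treatment variable into a predictor.

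Three stronger readings are tempting and are not supported:

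- **That IgG increase cannot be measured because serum IgG is taken at baseline only.** This holds for the routine safety panel. Research serum is requested at day 43, and the table of measurement times is in an additional file not shown here. That the article names no assay does not show that none is planned. In any case, sampling is not why the variable fails to identify who benefits; its post-randomisation nature is.
- **That overlap between arm and IgG increase damages the treatment estimate by a known factor.** The documents give no size for the IgG rise, and the treatment effect is estimated from the primary mixed model, which is described without IgG.
- **That the result would be used to select patients.** A rise known only after infusion cannot select anyone beforehand, and nothing in the article proposes this.

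**Conclusion.** The point holds as a minor one. The Secondary analysis section groups a consequence of IVIg with pre-randomisation factors for models with interaction terms. On the plain reading it is treated as an effect modifier, and in that role it cannot serve the objective of finding factors that predict benefit.

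That conclusion rests on the text alone. The size of any false signal rests on assumptions: with no confounding between IgG rise and prognosis, the test keeps its nominal level, and at assumed correlations of 0.5 and 0.8 it rejects in about 25% and 57% of trials. The documents give no information on which correlation applies.

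The primary analysis is unaffected. This is a wording improvement to an exploratory analysis, not a threat to the trial's main conclusion.

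**What to change.** In the Secondary analysis section, or in the statistical analysis plan that implements it:

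1. Restrict treatment-by-factor interaction models to pre-randomisation variables: disease duration, psychological baseline measures, allergy status and baseline IgG.
2. Take IgG increase out of that list. Report it separately, within the IVIg arm only, as an exploratory, non-randomised exposure-response association in patients with a follow-up sample.
3. Name the sample from which the follow-up IgG is taken. If it is the day 43 research serum, say so, and note that it is optional and drawn after the outcome window.

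The change is essentially wording. The price is precision and strength of inference: the within-arm analysis uses about half the patients, at most 108/2 = 54 and fewer where the second sample is missing, and it stays associational.
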